### Recruitment

Recruitment of potential participants will begin as follows: (1) informative posters providing a brief explanation of the study will be displayed around the main campus of the University of Zaragoza at tutoring whose services are used by students of distance courses (for UNED students) and other places of interest for university students to encourage interested students to make contact via e-mail; (2) contact will be made with different student organisations to send informative e-mails to students. Each organization will send the message using e-mail lists, without providing the research group with any personal information; and (3) contact with local government agencies and media (e.g., newspapers) to disseminate information about the research study and provide a contact e-mail for any interested students.

Those students who make e-mail contact will be provided with more detailed information by means of a phone call or virtual meeting. A research assistant will explain the study and verify that the student meets the inclusion criteria. This contact will also specify the route by which the study information document is to be received, and a link will be provided to the baseline evaluation. All assessments which will be made online, both at baseline and in the subsequent follow-up measurements at the end of the intervention (post-treatment), and at six months, and the surveys will be completed online using SurveyMonkey^®^. Before beginning the baseline survey, the participants will be able to read the information sheet, accept the privacy terms and conditions of the website, and sign the informed consent form. The recruitment and baseline assessment process will continue until the required sample size is obtained.

### Randomisation, allocation, and blinding

Once baseline data is collected, participants will be randomly allocated to each arm. The random assignment of the subjects will be carried out by a different member of the research group who is unrelated to the study and using a computer-generated random sequence. This sequence will be blinded to both the participants and the research assistants who will be assisting with the assessments (i.e., by providing the link to the survey on the appropriate date), as well as to the trial manager who will be in charge of group allocation. Participants will be assigned to one of two groups: ABCT or relaxation therapy. Given the nature of the interventions, neither the group facilitators (i.e., psychotherapists) nor the university student participants will be blinded to their allocation. However, the research assistant in charge of providing the link to the assessment survey will be blinded, as well as the expert who will carry out the statistical analysis.

### Data collection and monitoring

After completing the programmes, the same person who provided the links to complete the baseline survey will oversee the process of contacting the participants so that they can carry out the post-test (with a time window of one month after the intervention), and follow-up (six months after the last session of the programme, with a time window of one month) measurements. Participation in meditation programmes, as in the case of any psychotherapeutic approach, can cause negative side effects that, although rare, need to be monitored (Van Dam et al., 2018; Baer et al., 2021). Therefore, study participants will be asked to report any signs of a worsening in their mental or physical health (whether serious or not) that may arise during the sessions. Participants will also be asked to comment on any discomfort they experience both during and between sessions. If adverse effects appear, the psychologist in charge of the groups will discuss with an independent data monitoring committee (which will be made up of the trial manager, a clinical psychologist and a psychiatrist) whether any additional measures need to be taken to ensure the integrity of the participant (e.g., abandon the study). The results of the surveys at each time point will also be overseen by the data monitoring committee, who will decide whether any potential deterioration of psychological health needs further consideration or treatment. This will be facilitated by contacting the corresponding mental health services of national health system. Figure 1 is the flow diagram that shows the expected participation of the subjects throughout the study, from recruitment to follow-up data collection.

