**Methods and analysis:**

A two-arm RCT will be conducted involving 140 university undergraduate and postgraduate students from the University of Zaragoza and the National University of Distance Education (UNED) who reside in the autonomous community of Aragon, Spain. Interventions with either ABCT or relaxation therapy will be implemented, with an allocation ratio of 1:1 between groups. Both interventions will last six weeks and consist of six weekly group sessions lasting 1.5 h each. Data will be collected before and after the intervention, and there will be a follow-up at six months. The primary outcome will be psychological distress at post-intervention. Secondary outcomes will be depression, anxiety, stress and burnout symptoms, affectivity and emotional regulation. Attachment style, experiential avoidance, compassion (for others/oneself) and mindfulness skills will be measured as potential mechanistic variables. Intention-to-treat analysis will be performed using linear mixed regression models. The clinical significance of improvements will be calculated. Potential side effects will be monitored by an independent clinical psychologist.

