### Outcomes

Data will be collected using a battery of questionnaires administered at baseline, immediately after the intervention (post-treatment) and at six-month follow-up. Outcomes of the ABCT and the control conditions will be evaluated and compared. The primary outcome will be a self-reported global measure of psychological distress to provide data on the intervention. Secondary outcomes will allow a more detailed exploration of ABCT in terms of depression, anxiety, stress, burnout, emotional regulation and affectivity. Furthermore, the role of attachment style, experiential avoidance, compassion (for others/oneself) and mindfulness skills as potential mediators of outcome will be explored. A breakdown of the study outcomes is given in Table 3.

**Table 3 tab3:** Study outcomes.

Instrument	Assessment area	Kind of outcome	Time
Bespoke survey	Sociodemographic	Characteristics of participants	Baseline
DASS-21	Psychological distress	Primary (total score) Secondary (sub-scales) outcome	Baseline, post-treatment and 6-month follow-up
PANAS	Positive and negative affect	Secondary outcome	Baseline, post-treatment and 6-month follow-up
ERQ	Emotional regulation	Secondary outcome	Baseline, post-treatment and 6-month follow-up
MBI-SS	Burnout	Secondary outcome	Baseline, post-treatment and 6-month follow-up
RQ	Attachment style	Mechanistic measures	Baseline, post-treatment and 6-month follow-up
AAQ-II	Experiential avoidance	Mechanistic measures	Baseline, post-treatment and 6-month follow-up
SOCS-O	Compassion for others	Mechanistic measures	Baseline, post-treatment and 6-month follow-up
SOCS-S	Compassion for the self	Mechanistic measures	Baseline, post-treatment and 6-month follow-up
FFMQ-SF	Mindfulness	Mechanistic measures	Baseline, post-treatment and 6-month follow-up

DASS-21, depression, anxiety and stress scales, 21 items; PANAS, positive and negative affect schedule; ERQ, emotional regulation questionnaire; MBI-SS, Maslach burnout inventory student survey; RQ, relationship questionnaire; AAQ-II, acceptance and action questionnaire-II; SOCS-O, Sussex-Oxford compassion for others scale; SOCS-S, Sussex-Oxford compassion for the self scale; FFMQ-SF, Five facet mindfulness questionnaire short-form.

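### The Abstract and the Methods differ on who monitors side effects, and physical or other unwanted effects in students who stop attending have no stated reporting route

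*Protocol article*

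**What the plan says.** The Abstract (Methods and analysis) names one monitor: "Potential side effects will be monitored by an independent clinical psychologist".

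The Methods section Data collection and monitoring sets out three channels.

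- **Reports of worsening.** Participants are asked to report "any signs of a worsening in their mental or physical health (whether serious or not) that may arise during the sessions". The recipient of the report is not named.
- **Comments on discomfort.** "Participants will also be asked to comment on any discomfort they experience both during and between sessions".
- **Survey review.** The data monitoring committee looks at the survey results at each time point and decides whether a decline in psychological health needs follow-up.

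On escalation, the same section says: "If adverse effects appear, the psychologist in charge of the groups will discuss with an independent data monitoring committee". It describes the committee as one "which will be made up of the trial manager, a clinical psychologist and a psychiatrist". The section Randomisation, allocation, and blinding puts the trial manager in charge of group allocation and states that the group facilitators are not blinded.

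The Outcomes section describes the questionnaires: "Data will be collected using a battery of questionnaires administered at baseline, immediately after the intervention (post-treatment) and at six-month follow-up". Table 3 lists the instruments, and none of them asks about unwanted effects. According to Recruitment, all surveys are completed online.

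**The concern.** The Abstract tells the reader that someone independent watches for side effects. In the Methods, no independent psychologist has that task at the point where effects are first picked up. The psychologist in charge of the groups brings them to a committee, and one of its three members helps to run the trial.

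The two requests made directly to students are also framed around the sessions. A student who stops coming, possibly because a practice was upsetting, has left the setting to which those requests refer. If such effects are recorded less often than those of attenders, the reported harms are too low. If attendance or the habit of asking about difficulties differs between the programmes, the shortfall could differ by arm too.

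**Working it through.** No figure in the article is in dispute, so the check is a comparison of its statements, followed by two short calculations for scale.

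**1. Who monitors.** The Abstract names an independent clinical psychologist. Data collection and monitoring has the psychologist in charge of the groups taking adverse effects to a committee of a trial manager, a clinical psychologist and a psychiatrist. The committee's clinical psychologist may be the person the Abstract means. Even so, in the Methods that person deals with reported adverse effects only once the group psychologist raises them, and the committee called independent contains the trial manager. The two statements do not describe the same arrangement.

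**2. What each channel covers for a student who has stopped attending.**

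| Channel | Scope in the text | Reaches a student who has left? |
|---|---|---|
| Report of worsening | Mental or physical, "that may arise during the sessions" | No route stated |
| Comment on discomfort | During and between sessions | No route stated after leaving |
| Committee review of surveys | Psychological deterioration | Yes, if the survey is answered |

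The third channel does not depend on attendance. It is online, it is the same in both arms, and a blinded assistant sends the links. But its stated purpose is psychological deterioration, whereas the first channel covers physical health as well. A higher questionnaire score also does not show whether the student links the change to the programme or stopped because of it. What is left without a stated route is physical or other unwanted effects in students who leave and, for those who also do not answer the survey, psychological effects as well.

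**3. Scale of the group.** Inputs from Sample size: a loss of around 30% and about 190 students, 95 per arm.

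- 0.30 × 190 = 57 students in total; 0.30 × 95 = 28.5 per arm.
- On the Abstract's total of 140, 0.30 × 140 = 42.

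These figures show scale and do not estimate the gap. The article does not divide the 30% into students who stop sessions and students who do not answer surveys, and the two groups need not coincide.

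**4. Could capture differ by arm?** Assume that the same proportion p of students in each arm has an unwanted effect, that p is unrelated to leaving, and that only effects in retained students are recorded. With loss L in an arm, the recorded proportion is p × (1 − L), so the ratio between arms is (1 − L₁)/(1 − L₂), and p cancels.

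- Equal loss, 30% and 30%: 0.70/0.70 = 1.00.
- Unequal loss (assumed), 40% and 20%: 0.60/0.80 = 0.75.

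Under these assumptions, loss distorts the comparison only if it is unequal. The other possible source is a difference in how students are prompted. Table 2 lists a review of sensations and difficulties in every relaxation session and a sharing of homework experiences and doubts in sessions 2 to 6. Table 1 lists no matching item for attachment-based compassion therapy (ABCT). Since Table 1 is a summary of theory and practices, this shows that a difference is possible and does not establish one.

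**The case against.** The strongest reply is that the article already has a channel that does not depend on attendance. The committee's survey review is the same in both arms and would pick up psychological decline in a student who left but still answers. Discomfort between sessions is asked about as well. The Abstract's sentence can be read as a short form of a committee that is called independent and has a clinical psychologist on it. Adverse-event forms and raters are commonly left to a full protocol, which is not shown, and Table 3 is a list of outcomes, so the lack of a side-effect item there does not prove that none is collected.

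Much of this stands. Three stronger readings might be inferred, and the article does not support them.

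- **That harms of students who stop attending are missed.** The survey review contradicts this for psychological deterioration in those who respond.
- **That the arms are not comparable on harms.** The same procedure is written for both arms, the Data analysis plan contains no between-arm comparison of harms, and neither unequal loss nor unequal prompting is stated. That each arm's own facilitator handles the reports is also an inference: the text refers to the psychologist in charge of the groups, and does not say whether one person or two run the programmes.
- **That a given share of harms, such as half, would go unrecorded.** Any such figure needs rates among attenders and leavers that the article does not give, and would have to treat the whole 30% as unobserved.

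The reply does not remove two things. A fuller document cannot reconcile two differing statements within this article. And the wording that ties reports of worsening to the sessions is a stated rule, not merely a detail left out.

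**Conclusion.** The point holds in limited form. The Abstract and the Methods do not agree on who monitors side effects. As written, physical or other unwanted effects in students who stop attending have no stated route, so harms may be under-captured and capture could differ by arm.

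The size cannot be determined from the article. The 57 of 190 is only an indication of scale, and the range of 1.00 to 0.75 for relative capture rests on assumed loss rates. The primary endpoint, the DASS-21 total at post-treatment, is unaffected. This is a change worth making because it is cheap; it does not undermine the trial's main conclusion.

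**What to change.** 1. Reconcile the Abstract with Data collection and monitoring, so that both say who monitors side effects, who receives the reports, and in what sense the committee is independent given that the trial manager sits on it.
2. Add the same short set of questions on unwanted effects to the existing post-treatment and six-month online surveys. Cover mental and physical effects, and whether an effect was linked to stopping the programme.
3. Send these questions to every randomised student, whatever their attendance.
4. Report the answers by arm, with the number randomised and the number responding. Keep session reports as a separate safety signal and do not pool them with the survey answers.

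The cost is a few extra items in a survey already planned and some edited sentences. Students who do not answer the survey remain uncovered, but showing responders against the number randomised makes that gap visible.

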**Figure 1 fig1:**
[figure not shown]
Study flowchart.

### Interventions

Both groups will receive interventions with a duration of six weeks. Each session will be 90 min long and will be held in face-to-face groups. Before beginning the programme, participants will be given a paper copy of the information sheet and the informed consent form, and they will be able to raise any doubts they might have regarding the study.

#### Attachment-based compassion therapy

The ABCT programme that will be used is a short adaptation of the University of Zaragoza compassion training programme (García-Campayo et al., 2016). Table 1 shows how the sessions are structured in terms of theory as well as formal and informal practices. Tasks to consist of practical exercises using audio recordings will be set for completion between sessions. The ABCT programme will be conducted by a clinical psychologist with experience in ABCT and third generation therapies.

**Table 1 tab1:** Adaptation of the ABCT programme (6 weeks).

Session 1	Preparing for compassion: kind attention.	Theory: the functioning of our brain, the reality of suffering: primary and secondary suffering, what is and what is not compassion. Formal practices: compassionate breathing and compassionate body scan, compassionate coping with difficulties. Informal practices: 3-Minute compassion practice, self-compassion journal, savour and thank you
Session 2	Discovering our compassionate world	Theory: compassion and mindfulness, self-esteem and compassion, fear of compassion. Formal practices: connect with affection, develop a situation or a safe place, compassionate gesture and phrases. Informal practices: the object that unites us to the world, compassion practice diary, what are we good at?
Session 3	Developing our compassionate world	Theory: mechanisms of action of compassion, efficacy of compassion, self-criticism. Formal practices: identify and develop the secure attachment figure, replace the critical voice with the compassionate voice. Informal practices: write a letter to the attachment figure.
Session 4	Understanding our relationship with compassion	Theory: attachment models, importance of these models in daily life. Formal practices: becoming aware of our attachment model, receiving affection from friends, indifferent and enemies. Informal practices: Letter to parents
Session 5	Working on ourselves	Theory: importance of affection towards oneself and towards others Formal practices: giving affection to friends and indifferent, giving affection to ourselves, reconciliation with our parents. Informal practices: three positive and three negative aspects of our parents, the largest sample of affection (in general and from our parents)
Session 6	Understanding the importance of forgiveness	Theory: guilt and the importance of forgiveness Formal practices: become aware of the damage we have done to others and ask for forgiveness, forgive others, and give compassion to enemies, forgive oneself. Informal practices: compassion in daily life

#### Relaxation therapy

The progressive muscle relaxation programme proposed by Bernstein and Borkovec (1973) will be used. To match this programme to the ABCT programme, it will be adapted to six sessions, each lasting 90 min, with the addition of guided imagery. As in the previous case, tasks to consist of practical exercises using audio recordings will be also set for completion between sessions. The contents and structure of the sessions are described in Table 2. The relaxation program will be facilitated by a clinical psychologist with experience in relaxation techniques.

**Table 2 tab2:** Relaxation programme (6 weeks).

Session 1	Presentation of the group and the goals of relaxation Basic principles of progressive muscle relaxation Brief explanation of the initial procedure with 16 muscle groups Progressive muscle relaxation practice with 16 muscle groups Imagination training Identification of the sensations and difficulties of relaxation
Session 2	Share homework related experiences and doubts Theory of visualisation techniques Practice of progressive muscle relaxation with 16 muscle groups Visualisation Practice: The Orange Identification of sensations and difficulties of relaxation
Session 3	Share homework related experiences and doubts Brief explanation of the procedure with 7 muscle groups Practice of progressive muscle relaxation with 7 muscle groups Visualisation Practice: The Beach Identification of sensations and difficulties of relaxation
Session 4	Share homework related experiences and doubts Practice of progressive muscle relaxation with 7 muscle groups Visualisation practice: the landscape Identification of sensations and difficulties of relaxation
Session 5	Share homework related experiences and doubts Brief explanation of the procedure with 4 muscle groups Practice of progressive muscle relaxation with 4 muscle groups Visualisation practices: the globe and white light Identification of sensations and difficulties of relaxation
Session 6	Share homework related experiences and doubts Brief explanation of relaxation by evocation, relaxation by evocation + counting and relaxation by counting Relaxation by evocation + counting Relaxation by counting Mental relaxation and visualisation practice: the perfect day Identification of sensations and difficulties of relaxation

### Outcomes

Data will be collected using a battery of questionnaires administered at baseline, immediately after the intervention (post-treatment) and at six-month follow-up. Outcomes of the ABCT and the control conditions will be evaluated and compared. The primary outcome will be a self-reported global measure of psychological distress to provide data on the intervention. Secondary outcomes will allow a more detailed exploration of ABCT in terms of depression, anxiety, stress, burnout, emotional regulation and affectivity. Furthermore, the role of attachment style, experiential avoidance, compassion (for others/oneself) and mindfulness skills as potential mediators of outcome will be explored. A breakdown of the study outcomes is given in Table 3.

**Table 3 tab3:** Study outcomes.

Instrument	Assessment area	Kind of outcome	Time
Bespoke survey	Sociodemographic	Characteristics of participants	Baseline
DASS-21	Psychological distress	Primary (total score) Secondary (sub-scales) outcome	Baseline, post-treatment and 6-month follow-up
PANAS	Positive and negative affect	Secondary outcome	Baseline, post-treatment and 6-month follow-up
ERQ	Emotional regulation	Secondary outcome	Baseline, post-treatment and 6-month follow-up
MBI-SS	Burnout	Secondary outcome	Baseline, post-treatment and 6-month follow-up
RQ	Attachment style	Mechanistic measures	Baseline, post-treatment and 6-month follow-up
AAQ-II	Experiential avoidance	Mechanistic measures	Baseline, post-treatment and 6-month follow-up
SOCS-O	Compassion for others	Mechanistic measures	Baseline, post-treatment and 6-month follow-up
SOCS-S	Compassion for the self	Mechanistic measures	Baseline, post-treatment and 6-month follow-up
FFMQ-SF	Mindfulness	Mechanistic measures	Baseline, post-treatment and 6-month follow-up

DASS-21, depression, anxiety and stress scales, 21 items; PANAS, positive and negative affect schedule; ERQ, emotional regulation questionnaire; MBI-SS, Maslach burnout inventory student survey; RQ, relationship questionnaire; AAQ-II, acceptance and action questionnaire-II; SOCS-O, Sussex-Oxford compassion for others scale; SOCS-S, Sussex-Oxford compassion for the self scale; FFMQ-SF, Five facet mindfulness questionnaire short-form.

